### Cessation of total MRP and reintroduction of normal diet

Decision whether to stop the MRP will be made at week 8, if the participant has met the 50% excess weight loss target. If this target is not met, the participant will continue with MRP for a further 4 weeks to a total of 12 weeks.

### Maintenance of weight loss

Food reintroduction/maintenance phase (week 12 to month 12)Stepped food reintroduction or transition period (eg, carbohydrate and fat reintroduction for the low carb and low fat diet options) will be individualised to participants and delivered by Counterweight dieticians.Standard evidence-based behaviour change techniques including self-monitoring (of behaviours and behavioural outcomes), goal-setting and self-rewards, action-planning, problem-solving will be employed.Digital delivery with monthly dietitian/coach support, text chat (individual and group), in-app weekly monitoring and reminders will be available to participants for up to 12 months after completing the study. The dietitian/coach support is flexible and can be tailored to individual participants, based on their needs.

### Control group

The control group will receive standard care and dietary/exercise advice which will follow the National Health Service (NHS), National Institute for Health and Care Excellence and the European Society of Cardiology guidelines^18 26 63^ for promoting low-moderate intensity physical activity. BP and lipid management will adhere to clinical guidelines, with statin therapy adjusted based on CV risk.^63^ Health coaching advice will be provided to participants at baseline and follow-up visits.

### Study outcomes

Study endpoints are summarised in table 2 and discussed in brief below.

**Table 2 T2:** Summary or key trial objectives and endpoints

Primary objective	To investigate whether weight loss achieved with a low-energy MRP in obese adults with HF and preserved ejection fraction improves physical function (as determined by age, sex-adjusted Six-Minute Walk Test (6MWT) distance) compared with standard clinical care with attention control.
Secondary objectives	To examine the effect of MRP-mediated weight loss on: Reverse cardiovascular remodelling assessed at 12 weeks and 24 weeks. Improvement exercise capacity and preservation of muscle power. Improvement in HF symptoms and quality of life. Improvement in skeletal and muscle energetics. Improvement in metabolic profile. Physical activity as determined by accelerometery.
Primary end point	The change in distance walked during 6MWT between baseline and 12 weeks.
Primary imaging end point	Change in the left atrial volume indexed to height—between baseline and 12 weeks
Key secondary endpoints	Key changes in indices between baseline and 12 weeks: HFpEF symptoms: Kansas City Cardiomyopathy Questionnaire, Borg dyspnoea scale during exertion, SARC-F and Edmonton frailty scale. Body composition and adiposity including visceral and body adipose tissue volumes (determined on MRI). Key imaging endpoints include change in LV mass: volume, LV mass, LV mass/height, atrial volumes, systolic strain and diastolic strain rates, myocardial blood flow/perfusion reserve, extracellular volume, global myocardial perfusion reserve as a marker of microvascular function, circumferential and longitudinal PEDSR and myocardial systolic strain/strain rates (circumferential and longitudinal), arterial stiffness (mean ascending aortic distensibility). Echocardiographic mitral inflow velocity (E), myocardial relaxation (E’) and E/E’, a non-invasive marker of LV filling pressure. Diastolic dysfunction will be graded. Skeletal muscle strength. Levels of circulating fibroinflammatory biomarkers at baseline and postintervention. Daily physical activity behaviours as measured by accelerometery.
Exploratory	Qualitative data from semistructured interview. Skeletal and cardiac energetics assessed with 31P-MR spectroscopy. Proteomic, metabolomic and DNA samples analyses subject to additional funding.

HFheart failureHFpEFheart failure with preserved ejection fractionLVleft ventricularMRPmeal-replacement planSARC-FStrength, Assistance with walking, Rise from a chair, Climb stairs and Falls

#### Primary outcome

The trial’s primary outcome is the change in the distance traversed during the 6MWT (in metres) between baseline and 12 weeks.

The primary imaging outcome is the absolute change in the CMR-derived LAVi to height between baseline and 12 weeks.

#### Key secondary outcomes

The complete list of secondary outcomes is summarised in table 2. In summary, the key secondary outcomes will assess change between baseline and 12 weeks in the following:

Changes in body composition: change in body composition, visceral adiposity and body weight.Change in CV risk profile: change in BP measured with sphygmomanometer. Change in fasting glucose and glycaemic control (HbA1c) where applicable, lipid profile, markers of myocardial stress (troponin I and NT-proBNP levels). These outcomes will be measured with blood tests.Change in severity of symptoms of HFpEF will be assessed with a difference in KCCQ score.Change in markers of frailty will be assessed with a difference in EFS score, SARC F score.Change in sarcopenia measures will be assessed by measuring the absolute difference in the maximum handgrip strength test and MRI-derived SMI.

#### Key cardiac imaging secondary outcomes

Change in CMR-derived indices of LV remodelling (LV mass: volume ratio) and CMR-derived LV strain between baseline and 12 weeks.Change in CMR-derived MPR between baseline and 12 weeks.Change in echocardiogram derived E/e’ (measure of diastolic function) between baseline and 12 weeks.

#### Exploratory outcomes

Exploratory outcomes will be centred around the data from the optional qualitative interview, musculoskeletal and spectroscopy substudies.

Qualitative data from semistructured interview.Skeletal and cardiac energetics assessed with 31P-MRS.Proteomic, metabolomic and DNA analyses from blood samples (subject to additional funding).Skeletal muscle biopsy analysis for muscle fibre type and distribution, fat infiltration and inflammatory changes.

### Study reporting

On completion of the study, a Consolidated Standards of Reporting Trials diagram will be produced, which will include the number of patients: approached, consented, meeting eligibility criteria, reasons for exclusion, randomised and completing the study.

## Statistical methods and analysis

### Sample size calculation

The power calculation for 6MWT is based on an observational HFpEF study from our group where mean distance on 6MWT was 180±91.7 m.^64^ To detect a clinically meaningful difference of 55 m^65^,^67^ between MRP and control group, requires 88 subjects to complete the study (80% power at 0.05 significance level). Allowing for an overall drop-out of 20% (assuming up to 30% drop-out in the MRP arm and <10% drop-out in standard care), 110 participants will be recruited.

The CMR is powered to detect a 10 mL/m^2^ reduction in LAVi to body surface area and requires 44 participants per group. Additionally, detecting an improvement in MPR from 1.74±0.76 to 2.2±0.76, based on our pilot data, requires 42 participants per group. Therefore, a group of 110 will maintain >80% power (2-sided alpha, p<0.05) for LA volume indexed (allowing 20% drop out) and MPR (allowing 25% drop out).

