#### Cardiac Magnetic Resonance assessment of myocardial structure, function and perfusion

Following localisers, balanced steady-state free precession (bSSFP) LV cine images will be acquired in two-chamber, three-chamber and four-chamber views. Myocardial tissue will be characterised with a single T1 map (MOLLI) acquired at the junction of the basal/mid LV short-axis level and a single T2 map at junction of the basal/mid LV short-axis level acquired pre-contrast. Unless contraindicated, participants will undergo stress and rest perfusion with pharmacological vasodilator adenosine (140 µg/kg/min for 2–3 min). If a satisfactory haemodynamic response is not achieved (a drop in systolic BP of 10 mm Hg and/or a rise in heart rate of 10 bpm) after 2 min, the dose will be increased to a maximum of 210 µg/kg/min. During peak stress, a gadolinium-based contrast agent (gadoterate meglumine or gadobutrol, depending on availability at each recruitment site) will be injected (at 0.05 mmol/kg) at 5 mL/s, followed by a 20 mL bolus of normal saline. Data will be acquired using a multislice, free breathing saturation recovery pulse sequence with fast low-angle short readout acquired over 60 heart beats, in three short-axis slices as previously described.^41^ Myocardial blood flow (MBF) will be quantified using a dual pulse sequence acquisition with fully automatic inline calculations as previously described.^8 42^ Rest images will be performed approximately 10 min after stress with a further 0.05 mmol/kg bolus of contrast. In the meantime, short-axis stack images will be acquired using cine imaging (bSSFP) covering the entire LV. Late gadolinium-enhanced images (inversion recovery gradient echo sequence) and postcontrast T1 maps (MOLLI) will determine focal and diffuse myocardial scar, respectively. Aortic cine images will be acquired in the ascending and descending aorta at the level of the pulmonary artery bifurcation. Pulse pressure will be measured simultaneously to allow calculation of aortic distensibility which has been postulated to be the key determinant of LV remodelling in T2D.^43^

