#### Analysis of cardiac sequences

Cardiac volumes and mass, left and right ventricular stroke volume and ejection fraction will be calculated by PERSPECTUM.^37^ Experienced CMR analysts blinded to treatment allocation will use CVi42 (Cardiovascular Imaging, Canada) to manually trace the endocardial borders in the end-diastolic and end-systolic phases in each of the short-axis views, following the standard UK Biobank evaluation approach.^44^ This analysis will produce, for both the left and the right ventricle the end diastolic volume, end systolic volume, stroke volume and ejection fraction. Additionally, LV muscle mass and wall thickness will be determined from the function data.

Analysis of LV strain, quantitative analysis of perfusion data, calculation of the extracellular volume (ECV) will be performed by an experienced operator in Leicester using CVI42 software. Assessment of peak diastolic filling rate, systolic global longitudinal and circumferential strain, global longitudinal strain and circumferential and longitudinal peak early diastolic strain rates will be performed as previously described.^35^ Epicardial adipose tissue volume will be quantified in cubic centimetres.

Late gadolinium enhancement will be qualitatively assessed in all 16 segments of the American Heart Association model by an expert CMR cardiologist as per the Society for Cardiac Magnetic Resonance guidance.^45^ For ECV calculation, a single region of interest will be manually drawn in the LV septum of the short axis on the native and postcontrast T1 maps, as previously described.^46^ Segments containing myocardial infarction or non-ischaemic enhancement (as judged by an experienced CMR expert) will be excluded.^47^ ECV value will be calculated using the previously described formula.^46^

Quantitative analysis of perfusion data will be performed as previously described using an automated AI tool.^41^ The myocardial perfusion maps will be visually inspected for quality and discarded if errors are found. The MBF values for each of the 16 myocardial segments will be recorded for stress and rest, and global values will be automatically calculated as averages. Rate pressure product (RPP) will be calculated (heart rate×systolic BP) and rest MBF will be corrected for RPP as per best practice.^48^ Myocardial perfusion reserve (MPR) will then be automatically calculated for each segment as stress MBF/rest MBF and results recorded.^41^

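### The 25% drop-out allowance for myocardial perfusion reserve (MPR) does not fit 110 recruits: it leaves 82.5 completers, below the plan's own 84, with power of about 77–78% instead of above 80%

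*Protocol article*

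**What the plan says.** The Sample size calculation section of the protocol article sizes three endpoints.

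- **Six-minute walk test (6MWT), the primary endpoint:** 88 completers and 20% overall drop-out, so that "110 participants will be recruited".
- **Left atrial volume index (LAVi):** 44 per group.
- **MPR:** "detecting an improvement in MPR from 1.74±0.76 to 2.2±0.76, based on our pilot data, requires 42 participants per group".

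It then concludes that "a group of 110 will maintain >80% power (2-sided alpha, p<0.05"), and applies this "for LA volume indexed (allowing 20% drop out) and MPR (allowing 25% drop out").

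MPR is listed under Key cardiac imaging secondary outcomes. It is neither the primary endpoint nor the primary imaging endpoint. The Statistical analysis section plans linear regression with the stratification factors for the key secondary outcomes.

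**The concern.** The sentence offers a safety margin: a quarter of participants could be lost and MPR would still be powered above 80%. That can be checked against the number per group printed just before it, and it fails. A reader who relied on it could take a null MPR result at 25% loss as coming from a comparison with at least the conventional power, when power would be a little lower.

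The margin is also more likely to be used for MPR than for the 6MWT, because MPR can be missing for reasons other than drop-out. Perfusion is conditional ("Unless contraindicated, participants will undergo stress and rest perfusion with pharmacological vasodilator adenosine"), and afterwards "The myocardial perfusion maps will be visually inspected for quality and discarded if errors are found".

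**Working it through.** **Inputs, all from the Sample size calculation section unless noted**
- MPR means 1.74 and 2.2, so the difference is 0.46; SD 0.76
- Two-sided alpha 0.05; target power 80%
- Stated need: 42 per group, 84 in total
- Recruited: 110, allocated 1:1 (Randomisation section), so 55 per arm
- MPR drop-out allowance 25%; overall trial drop-out 20%, with up to 30% in the meal-replacement arm and under 10% in the control arm

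**Step 1: reproduce the 42 per group**

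n per arm = 2 × [(1.960 + 0.842) × SD / difference]²
= 2 × (2.802 × 0.76 / 0.46)² = 42.85, so 43.

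The two-sample t-test gives 43.83, so 44. The stated 42 is one or two below.

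**Step 2: apply the 25% loss**

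110 × 0.75 = 82.5, or 41.25 per arm. This is 1.5 below the plan's own 84. Read the other way:
- 84 completers at 25% loss need 84 / 0.75 = 112 recruits.
- With 110 recruits, the largest loss that keeps 84 is 1 − 84/110 = 23.6%.

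LAVi closes under the same check: 2 × 44 = 88, and 88 / 0.80 = 110.

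**Step 3: power at the resulting numbers**

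Normal approximation: power = Φ( 0.46 / [0.76 × √(2/n)] − 1.960 ).

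Example at n = 41: 0.76 × √(2/41) = 0.1679; 0.46 / 0.1679 = 2.740; 2.740 − 1.960 = 0.780; Φ(0.780) = 78.2%.

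| Per arm | Situation | Normal | t-test |
|---|---|---|---|
| 41 | 25% loss, rounded down | 78.2% | 77.3% |
| 41.25 | 25% loss, exact | 78.5% | 77.5% |
| 42 | number stated in the plan | 79.2% | 78.3% |
| 43 | normal-formula requirement | 80.1% | 79.2% |
| 44 | 20% loss, equal arms | 81.0% | 80.2% |

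**Step 4: how much loss 110 can absorb**
- Keep 86 completers (2 × 43, normal): 1 − 86/110 = 21.8%
- Keep 88 completers (2 × 44, t-test): 1 − 88/110 = 20.0%

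**Step 5: uneven loss**

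If the 20% falls at the plan's outer limits of 30% and 10%, the arms hold 55 × 0.70 = 38.5 and 55 × 0.90 = 49.5. Power is then 80.4% (normal) or 79.5% (t-test), against 81.0% and 80.2% with equal arms. Uneven loss matters by less than one point.

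**The case against.** The strongest defence has four parts.

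1. **The 42 is not a mistake.** A reader might infer that the per-group number is miscalculated. The documents do not support that. The second mean is printed to one decimal. If it were 2.205 before rounding, the difference would be 0.465 and the formula gives 41.93, so 42. Rounding can also go the other way (a difference of 0.45 needs 45 by the normal formula), and the unrounded pilot values are not shown. A gap of one or two participants cannot be called an error on these figures. This part stands.

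2. **The planned analysis may be more efficient than an unadjusted comparison.** If the covariates correlate with the outcome at about 0.21 (normal) or 0.26 (t-test), power at 41 per arm reaches 80%. That is an assumption. The article states no such correlation, and for secondary outcomes it names the stratification factors without naming baseline MPR. The gain is possible but cannot be credited to the stated figure.

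3. **At the trial's own overall drop-out of 20%, MPR is powered as claimed.** With equal arms this is so: 81.0% or 80.2%. A reader might infer that there is no margin at all, and that would be too strong. There is one, of about 20 to 22% rather than 25%.

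4. **Losses peculiar to perfusion imaging.** A reader might infer that contraindications and discarded maps push power well below 77%. The article gives no rate for either. It also already allows five points more loss for MPR than for LAVi, which may be meant to cover them. No further reduction can be calculated from the documents.

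None of this removes the mismatch in Step 2, which uses only the plan's own 42, 110 and 25% and holds even if 42 is accepted as correct.

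**Conclusion.** The concern holds in a limited form. Recruiting 110 and losing 25% leaves 82.5 participants, short of the 84 the plan requires. On the printed inputs, power for MPR is then about 77–78%, not above 80%. The shortfall is about 1.5 to 3 points.

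This rests on the printed difference of 0.46, on an SD of 0.76 applying to the quantity compared, on a two-sided 0.05 level, on roughly equal arms, and on an unadjusted two-group comparison. The mismatch between 82.5 and 84 needs none of the power assumptions.

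The consequence is small. MPR is a secondary imaging endpoint. The 110 follows from the 6MWT (88 / 0.80 = 110) and does not depend on MPR. The Discussion already warns that sizing on the 6MWT may limit the evaluation of secondary endpoints. What needs correcting is a stated power that the stated numbers do not deliver.

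**What to change.** Change the MPR clause in the Sample size calculation section in one of two ways.

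- **Restate the allowance as 20%.** This gives 44 per arm and power of 81.0% (normal) or 80.2% (t-test) with equal arms. About 22% is the most that keeps 80% by the normal approximation, and 23.6% the most that keeps 84 completers.
- **Keep 25% and state power as about 77–78%.** This is the more candid choice if the extra five points over LAVi were meant to cover contraindicated or unusable perfusion studies, since a 20% allowance equals the trial's overall drop-out and leaves no room for them.

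If the 42 is being edited anyway, 43 (normal) or 44 (t-test) matches the printed inputs, but this is optional.

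The cost is one sentence of text and a slightly less favourable statement for one secondary endpoint. Recruitment, design and analysis do not change.

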### Statistical analysis

The distribution of data will be assessed for normality using histograms, the Shapiro-Wilk test and Q-Q plots. Descriptive statistics will be used to characterise the groups comprising only those participants who have completed the trial, as per the per-protocol analysis criteria. Continuous data will be expressed as mean (±SD), if normally distributed or median (IQR 25%–75%) if not. Categorical variables will be reported as count and percentage. For the analysis of the primary outcome, the MRP group will be compared with the control group, using linear regression adjusted for stratification factors (sex, ethnicity and baseline SGLT2-i use) and baseline distance walked during 6MWT. The treatment effect will be presented as a point estimate, 95% confidence intervals and p value. Changes in the key secondary outcomes will also be assessed using linear regression with the same stratification factors as the primary outcome.

Additionally, the relationships between clinical and imaging markers (cardiac function, adiposity and skeletal myopathy) at baseline and their changes will be correlated with exercise capacity and changes therein among completers. Multivariate regression analyses will be employed to discern significant independent predictors of outcomes. To ensure methodological rigour, a comprehensive statistical analysis plan will be developed and formally approved by the study statistician before the commencement of these analyses.

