### Randomisation

Randomisation (1:1) will occur at the end of the baseline visit after data collection, using the ‘blockrand’ package in R^61^within the REDCap (Research Electronic Database Capture) system . The allocation list will be concealed from the user and non-editable once uploaded. REDCap’s randomisation module will reveal participant allocation only at the moment of randomisation, ensuring strict allocation concealment. The randomisation will be stratified by sex, ethnicity and baseline SGLT2-i use.

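### The secondary change models, as written, omit each outcome's own baseline value; separately, the primary objective names an age adjustment that the primary model lacks

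*Protocol article*

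**What the plan says.** The Statistical analysis section of the protocol article specifies two models in adjacent sentences. The primary outcome is analysed "using linear regression adjusted for stratification factors (sex, ethnicity and baseline SGLT2-i use) and baseline distance walked during 6MWT". The next model is given as: "Changes in the key secondary outcomes will also be assessed using linear regression with the same stratification factors as the primary outcome". The first sentence lists the stratification factors and the baseline value as two separate items. The second carries over only the former.

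The outcomes affected are those in Table 2 and under the two secondary-outcome headings: KCCQ, body composition, LV remodelling and strain, MPR, E/e′ and others. The primary imaging endpoint, left atrial volume indexed to height (LAVi/height), is listed apart from these and has no model sentence of its own.

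On power, the Sample size calculation section says that "a group of 110 will maintain >80% power (2-sided alpha, p<0.05) for LA volume indexed", and the same sentence goes on to make the claim for MPR.

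On age, Table 2 words the primary objective as physical function "as determined by age, sex-adjusted Six-Minute Walk Test (6MWT) distance". The Primary outcome section defines the endpoint as a plain change in metres. Age is neither a stratification factor (Randomisation section) nor a covariate in the primary model.

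**The concern.** A change score analysed without its baseline fixes the slope of follow-up on baseline at 1. With equal SDs the true slope is ρ, so whenever ρ is below 1 the model leaves avoidable noise in the estimate. It also leaves the estimate exposed to chance baseline differences between arms: the arm that starts higher tends to fall more. Stratifying on sex, ethnicity and SGLT2-inhibitor use does not balance baseline MPR or KCCQ. With about 44 completers per arm, such differences will occur on some of the many secondary outcomes.

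At stake are the precision of the mechanistic and symptom results, which are much of the trial's purpose, and possibly the stated power for MPR. The age wording raises a different issue: the objective and the model for the primary outcome do not describe the same analysis.

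**Working it through.** **The plan's own figures.** Inputs from the Sample size calculation and Randomisation sections: SD 91.7 m (a cross-sectional SD of distance), difference 55 m, α 0.05 (two-sided is stated for the imaging endpoints and assumed here too), power 80%, 1:1 allocation. With (1.960 + 0.842)² = 7.849:

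- 6MWT: n per arm = 2 × 7.849 × (91.7/55)² = 43.6, so 44 per arm and 88 in total. 88/0.80 = 110. Both stated figures reproduce.
- MPR: difference 2.2 − 1.74 = 0.46, SD 0.76. n per arm = 2 × 7.849 × (0.76/0.46)² = 42.85, so 43 against the stated 42, close enough.

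Both calculations are unadjusted two-sample comparisons on a cross-sectional SD.

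**Variance with and without the baseline.** Let s be the common SD at both visits and ρ the baseline/follow-up correlation. Both are assumptions: the article gives no ρ and does not say the SDs are equal. ρ is best read as the correlation within strata.

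- Change score: variance 2(1 − ρ)s²
- Baseline-adjusted: variance (1 − ρ²)s²
- Ratio: 2/(1 + ρ)

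MPR power uses 44 per arm, difference 0.46 and s = 0.76, by normal approximation. For example, at ρ = 0.3 without baseline, the SE is 0.76 × √1.4 × √(2/44) = 0.192. Then 0.46/0.192 = 2.40, and Φ(2.40 − 1.96) = 0.67.

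| ρ (assumed) | Variance ratio | SE ratio | MPR power without baseline | MPR power with baseline | MPR n per arm for 80%, without / with |
|---|---|---|---|---|---|
| 0.3 | 1.54 | 1.24 | 67% | 85% | 60 / 39 |
| 0.5 | 1.33 | 1.15 | 81% | 91% | 43 / 33 |
| 0.7 | 1.18 | 1.08 | 96% | 98% | 26 / 22 |
| 0.9 | 1.05 | 1.03 | >99% | >99% | 9 / 9 |

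The change score reaches 80% power for MPR at 44 per arm when 42.85 × 2(1 − ρ) = 44, that is at ρ = 0.49. With the 25% drop-out the article allows for MPR (82.5 completers, 41.25 per arm) the crossing point is ρ = 0.52. Hence about 0.5.

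**Cost of the extra covariate.** With 88 completers, and ethnicity entered as one term, residual degrees of freedom fall from 83 to 82. That raises the SE by √(83/82) = 1.006, about 1.2% in variance, so the gain disappears only when ρ exceeds about 0.98.

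**Shift under chance imbalance.** The SE of a baseline difference at 44 per arm is √(2/44) = 0.213 SD. A one-SE imbalance moves the change-score estimate by (1 − ρ) × 0.213 SD, which is 0.107 SD at ρ = 0.5. For MPR that is 0.107 × 0.76 = 0.08, or 18% of the 0.46 target.

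**Age in the primary model.** The partial R² of age, given baseline distance and strata, is not in the article. At assumed values of 0, 0.01, 0.02, 0.05 and 0.10, adding age multiplies the SE, √[(1 − R²) × 83/82], by 1.006, 1.001, 0.996, 0.981 and 0.955.

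**The case against.** The secondary sentence may be shorthand for the full primary model: it follows directly and links back to it. That is possible. But the primary sentence keeps strata and baseline apart and the secondary one names only strata, so if shorthand was meant the wording still needs correcting. The Abstract does not settle the matter. It lists only the randomisation factors, but it omits baseline even for the primary outcome, where baseline is certainly used.

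Four stronger readings are tempting, and the article does not support them.

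- A reader might infer that the secondary estimates are biased or the tests invalid. They are not: a randomised change-score comparison is unbiased over randomisations with correct type I error. The 0.107 SD shift above is conditional on an imbalance and is half of the change score's own SE at ρ = 0.5 (0.213 SD).
- A reader might infer that the imaging power claim fails. The plan took no credit for baseline adjustment, so at ρ of 0.5 or more the change score roughly meets or exceeds the planned MPR power. A shortfall needs a lower ρ.
- A reader might infer that LAVi/height will be analysed without its baseline. No model is written for it. A fuller analysis plan is promised and may supply one, so the silence is not an error.
- A reader might infer that omitting age costs the primary analysis material precision. Once baseline distance is in the model, the SE changes by between +0.6% and −4.5% over the range shown, and nothing in the article says where in that range it lies.

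**Conclusion.** The point holds as a matter of efficiency and wording. The secondary model that the article states is less precise than the one it uses for the primary outcome. The loss is material at ρ of 0.3 to 0.7 (variance 54% to 18% larger) and small at 0.9 (5%). These sizes rest on an assumed ρ and equal SDs. The stated MPR power is at risk only below ρ of about 0.5. The sample size of 88 completers and 110 recruited is unaffected.

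The age wording is a genuine mismatch between the objective on one side and the endpoint and model on the other. It is a point of consistency. The phrase could also be read as a predicted-distance scale, which would conflict with an endpoint in metres, so it should be resolved before analysis.

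**What to change.** 1. Replace the secondary-model sentence with one stating that each continuous secondary and imaging outcome is analysed by linear regression of its change (or week-12 value) on arm, its own baseline value and the stratification factors. Name LAVi/height explicitly for clarity. The cost is one sentence and one degree of freedom per model. The main secondary and imaging assessments are already scheduled at baseline in Table 1.
2. Reconcile Table 2 with the primary model, either by adding age as a continuous covariate or by removing the age and sex adjustment from the wording of the objective. Either is acceptable if settled before the analysis; adding age costs one further degree of freedom, and no precision gain need be claimed for it.

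Neither change alters the sample size or data collection.
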